### Statistical Analysis

The treatment outcomes will be collected via our Health Insurance Portability and Accountability Act–compliant medical record platform and will be extracted by trained research personnel. Descriptive statistics will be used to describe patient characteristics and demographics of our patients and treatment outcomes defined in Table 1. To examine any differences in effectiveness between the 2 interventions, we will compare the rate of weight change between the groups using generalized linear models in R version 4.1.1 (R Core Team). We will also look at outcomes across ED subtypes.

### Procedures

Upon beginning treatment at Equip Health, eligible patients will be randomly assigned to receive either the calorie-based approach or the Plate-by-Plate intervention within their first 1-2 sessions with their assigned RD. In the first phase of treatment, the RD meets exclusively with caregivers (eg, parents or guardians) at a weekly meeting cadence for the first month, and thereafter in accordance with the RD’s judgment.

A high-level summary of each approach is as follows: (1) calorie-based nutrition prescription: following the completion of a nutrition assessment by the RD, caregivers will be prescribed a calorie goal and be instructed to aim to reach that goal daily as a primary focus of treatment. In collaboration with caregivers, a calorie goal will be assigned to 3 meals and 3 snacks daily. For example, the goal may be 3000 kcal per day, comprised of 700 kcal meals 3 times per day, and 300-kcal snacks 3 times per day. Additionally, caregivers are provided 7-day sample menus that align with their calorie prescription. If clinically indicated, they may also receive education on how to increase the caloric density of meals while maintaining low volume. Adjustments will be made throughout the treatment course to calorie prescriptions per RD’s judgment to accommodate the weight restoration goal of 2 lbs per week. During the initial session, caregivers are instructed to send photos and density estimates of all foods consumed by the child to the RD, and feedback will be given speaking to the adequacy of calorie content of meals and snacks in the follow-up sessions. (2) Plate-by-Plate approach is summarized for caregivers in the following steps:

Choose 10-inch platePlate all food groupsFill plateParent decides number of meals or snacksInclude varietyDoes the meal make sense?Final review: Does the plate make sense?

Caregivers are instructed to prompt the patient to complete the plate, and in the case of food refusal, oral supplements are provided to replace the remaining food.

### Training and Fidelity

All Equip RDs have experience in treating EDs using a variety of dietary interventions within and outside of the FBT framework. Upon hiring, Equip RDs complete an in-depth video training on various interventions commonly used in ED treatment, including the Plate-by-Plate approach and calorie-based meal plans. RD interventionists undergo a live training session overviewing study protocols and each intervention, and a prerecorded training on the Plate-by-Plate intervention (led by authors of the Plate-by-Plate intervention). Interventionists will receive ongoing training as needed and supervision to ensure adherence to the respective approaches and will additionally be trained to notify research staff of any fidelity issues or protocol deviations by other providers on a treatment team.

Electronic records will be reviewed by study personnel on a weekly basis to ensure adherence to the assigned treatment approach. Specifically, session documentation, chat communications, and any document exchanges will be reviewed. Any fidelity issues (and the subsequent potential need for participant withdrawal) will be discussed by research personnel and interventionists. Further, should a patient discharge prior to week 8 of treatment, or if the RD determines that the assigned intervention is a poor fit for the patient, the patient may be withdrawn.

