**Secondary outcomes**			
	Eating Disorder Examination Questionnaire Short Form	Global total score, Eating concern scale score, Weight concern scale score, and Shape concern scale score	Upon admission, weekly thereafter (baseline and week 8)
	Burden Assessment Scale	Caregiver burnout	Every 40 days (baseline and week 8)
	Parent versus Eating Disorders	Caregiver self-efficacy	Day 14, every 40 days thereafter (baseline and week 8)
	Patient Health Questionnaire	Symptoms of depression	Upon admission, monthly thereafter (baseline and week 8)
	Generalized Anxiety Disorder Scale	Symptoms of anxiety	Upon admission, monthly thereafter (baseline and week 8)
	Clinician semistructured interview	Acceptability and perceived effectiveness of intervention	End of study
	Caregiver semistructured interview	Acceptability and perceived effectiveness of intervention	Treatment week 8 (approximate)

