#### Weight

Upon admission, caregivers receive instructions from their assigned Equip medical provider on proper procedure for checking weight. Weights are taken in the morning, after voiding, prior to any oral intake and patients are asked to wear light clothing. The patient’s weight (in pounds) is taken twice weekly by caregivers and communicated via text message from caregivers to Equip’s Health Insurance Portability and Accountability Act–compliant medical record platform. For each patient, the RD calculates a target weight for weight restoration. Target weight is calculated using expected weight data from each patient’s CDC BMI-for-age Growth Charts. Our primary end point of interest is weight change during the first 8 weeks of treatment, which will include an average weekly rate of weight gain and total weight change from admission to treatment week 8.

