## Discussion

### Strengths and Limitations

To our knowledge, this will be the first comparison of digitally delivered dietary interventions for the treatment of EDs. Given access issues faced by patients seeking ED treatment, and increasing acceptability and use of telehealth, it is of particular value to test interventions in the digital space. Testing assumptions upon which approaches are developed is also valuable as we were able to gain insights that help us tailor approaches that better resonate with caregivers and providers.

It should be noted that the majority of patients who present for ED treatment at Equip have engaged with numerous prior programs and providers, and as such, they may have encountered various dietary approaches. While it was not realistic nor warranted to exclude those with prior treatment histories, we addressed this by instructing RD interventionists to notify study personnel should it prohibitive to orient caregivers to the assigned approach. At that point, a determination will be made as to whether the patient should be withdrawn from the study. Further, although with FBT caregivers are tasked with renourishing their child between ages 6 and 24 years, it is possible that there may be differences in intervention across age ranges, particularly for patient-facing interventions. However, it should be noted that individual (patient) nutrition therapy is provided only in later stages of FBT (generally following several months of nutritional restoration).

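### Patients may be withdrawn from the study after randomisation at the discretion of staff who know the arm; if they are then dropped, the week-8 weight comparison can be biased

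*Protocol article*

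**What the plan says.** Patients are randomised early. Under Procedures, "eligible patients will be randomly assigned to receive either the calorie-based approach or the Plate-by-Plate intervention within their first 1-2 sessions" with the dietitian (RD); Group Assignment places assignment at admission. On either reading, the withdrawal rules operate after randomisation.

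Training and Fidelity gives three grounds for withdrawal:
- Fidelity: "Any fidelity issues (and the subsequent potential need for participant withdrawal) will be discussed by research personnel and interventionists".
- Early discharge: "should a patient discharge prior to week 8 of treatment", the patient may be withdrawn.
- Poor fit: "if the RD determines that the assigned intervention is a poor fit for the patient, the patient may be withdrawn".

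Strengths and Limitations adds a fourth. If it proves prohibitive to orient caregivers to the assigned approach, the RD tells study personnel, and "a determination will be made as to whether the patient should be withdrawn from the study". This sentence shows that withdrawal can mean leaving the study, not only leaving the dietary approach.

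On the outcome, the Weight section states: "Our primary end point of interest is weight change during the first 8 weeks of treatment". On the analysis, the Statistical Analysis section states: "we will compare the rate of weight change between the groups using generalized linear models in R version 4.1.1". It names no analysis set. Table 1 places the caregiver interview at about treatment week 8.

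**The concern.** All four grounds arise between randomisation and the primary time point. Poor fit and failure to orient caregivers are defined by how the assigned approach is going, and fidelity problems are defined by adherence to it. The RD who delivers the approach judges fit, and takes part in or triggers the decision on fidelity and orientation. No objective criterion is given.

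The article also gives a reason why withdrawal might differ by arm. Participant Selection notes that patients with ARFID may accept very few foods, which could make multi-component meals hard to present, and such meals are central to Plate-by-Plate.

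If withdrawn patients are dropped and they tend to be low gainers, the arm that loses more of them looks better than it is. This matters because the Significance section hopes to identify a preferred or best-practice approach and to describe differences between AN and ARFID.

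Acceptability is a stated aim as well. Families who stop before week 8 know most about why an approach was not acceptable. The article makes no specific provision for interviewing them, so they may be under-represented.

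**Working it through.** The article states no power, effect size, SD or withdrawal rate, so there is no figure of its own to reproduce. What follows illustrates how large the problem could be.

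**Inputs from the article.** 50 patients per arm; 16% of the 100 have ARFID (Demographics).

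**Assumptions.** Weight change is normal with SD 1, so results are in SD units. There is no true difference. A share *w* of each arm is withdrawn and dropped. The tendency to stay has correlation *ρ* with weight gain. The test is a two-sided t test at 5%.

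**Yardstick.** The difference detectable with 80% power and 50 per arm is (1.960 + 0.842) × √(2/50) = 2.802 × 0.200 = 0.56 SD. With 20% dropped from each arm (40 left) it is 2.802 × √(2/40) = 0.63 SD.

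**Bias formula.** Dropping the lower tail raises an arm's mean by ρ·φ(z_w)/(1 − w), where φ is the standard normal density and z_w the w-quantile. The between-arm bias is the difference of the two terms.

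- w = 10%: 0.1755/0.90 = 0.195
- w = 20%: 0.2800/0.80 = 0.350
- w = 30%: 0.3477/0.70 = 0.497

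For 20% versus 10%, the bias is 0.350 − 0.195 = 0.155 SD at ρ = 1 and half of that, 0.077 SD, at ρ = 0.5. Simulation with 10,000 trials per row agrees:

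| Withdrawn, arm A v arm B | ρ | Bias, formula (SD) | Bias, simulated (SD) | False positives |
|---|---|---|---|---|
| 20% v 20% | 0.5 | 0 | 0.002 | 4.6% |
| 20% v 20% | 1.0 | 0 | −0.001 | 4.9% |
| 20% v 10% | 0 | 0 | 0.003 | 4.6% |
| 20% v 10% | 0.5 | 0.077 | 0.082 | 6.6% |
| 20% v 10% | 1.0 | 0.155 | 0.152 | 13.5% |
| 30% v 10% | 0.5 | 0.151 | 0.149 | 10.5% |
| 30% v 10% | 1.0 | 0.302 | 0.305 | 39.3% |

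A separate simulation (8,000 trials) with withdrawal in one arm only gave 0.19 SD and 18% false positives at 10% v 0% with ρ = 1, and 0.24 SD and 22% at 20% v 0% with ρ = 0.7.

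**Reading.** At 20% v 10% the bias is 0.077/0.56 = 14% to 0.155/0.56 = 28% of the detectable difference. It vanishes if withdrawal is unrelated to weight gain, or is equal in both arms by the same mechanism.

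**How much could ARFID alone contribute?** An even split gives about 8 ARFID patients per arm. If half of those in one arm were withdrawn, that is 4/50 = 8% of the arm, a gap close to the 10 points in the 20% v 10% rows.

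**The case against.** A reader might infer that the arm comparison covers only patients for whom the approach worked, and is therefore biased. The article does not support that, for three reasons.

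- It never says that withdrawn patients are excluded. The analysis set may be defined in a full protocol or analysis plan that is not shown, and its absence from an article is no error. Clinical measures continue throughout treatment as standard practice (Assessments and Measures), so weights may exist for withdrawn patients who remain in treatment.
- Withdrawal is optional on every ground, and none is triggered by poor weight gain, so poor gainers can stay.
- Not every ground reflects response to the approach. Reportable problems include deviations by other providers on the team, no reason is attached to early discharge, and difficulty in orienting caregivers is linked to approaches met in earlier treatment.

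A reader might also infer that withdrawn families lose the caregiver interview. Nothing says so: the interview section excludes nobody and offers a web form to caregivers who do not respond. The RD interviews can also bring out poor fit.

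Finally, the same rules apply to both arms, and the study describes itself as a feasibility study of preliminary effectiveness.

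These points limit the claim to a conditional one. They do not remove it. Withdrawal from the study is a rule of conduct that the article states. Unless follow-up is expressly kept, an analysis set defined later may lack the questionnaires and interviews it needs.

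**Conclusion.** The concern stands in conditional form. The article permits discretionary withdrawal from the study after randomisation, by or with staff who know the arm, on grounds partly tied to the assigned approach, and nothing in it protects an as-randomised comparison. If withdrawn patients are dropped, the primary comparison can be biased. That requires withdrawal to be related to weight gain and to differ by arm. The ARFID remark makes a difference between arms possible but does not establish it.

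The size ranges from zero, through about 0.08 to 0.15 SD with 7% to 14% false positives at 20% v 10%, to about 0.3 SD with 39% in the most extreme two-arm case shown. Every rate and correlation is assumed. Under-representation of early-stopping families in the caregiver interviews is likewise a risk, not a stated fact.

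**What to change.** - State that poor fit, fidelity problems or stopping the assigned approach do not end study follow-up. This concerns follow-up and analysis only; it sets no rule on when a patient should change dietary approach.
- Keep using the twice-weekly weights recorded in routine care, up to week 8 or discharge.
- Analyse all 100 patients in the arm to which they were randomised. Any as-treated or per-protocol analysis is a sensitivity analysis.
- Report withdrawals, changes of approach and discharges before week 8, with reasons and by arm, as acceptability outcomes.
- Offer the existing interview or web form to families who stop early.

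**Cost.** Mostly wording, since the weights are already in the medical record. Keeping everyone in the assigned arm dilutes the as-delivered contrast somewhat, and there are a few more interviews or forms. The article expected data collection to end by November 2022, so extra interviews may no longer be possible. The analysis and reporting changes can still be made with the weights and withdrawal reasons on record.

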## Results

### Demographics

A total of 100 patients (with average age of 15 years) were enrolled on a rolling basis from March through August 2022. Fifty patients were assigned to the Plate-by-Plate group and 50 to the calorie target group. Overall, 83% of participants were cisgender females, 9% were cisgender males, 6% were nonbinary, and 2% were transgender. Furthermore, 66% of participants were diagnosed with AN restricting subtype, 18% with the AN binge-purge subtype, and 16% with ARFID. We anticipate completion of data collection by November 2022 and analysis by January 2023.

### Significance

We anticipate that, following completion of this study, we will be able to (1) address common myths, assumptions, and misconceptions associated with each intervention; (2) identify differences in outcomes and emerging themes from interview data, and use findings to adapt interventions and the supporting digital resources; (3) identify a preferred, or “best practice” approach for improving outcomes in the early phase of FBT, as early response is predictive of remission; and (4) understand any potential differences or nuances that may exist by intervention across the 2 ED subtypes (AN and ARFID).

### Design Considerations

While a variety of interventions may be used in practice, we selected Plate-by-Plate and calorie-based approaches due to their common use in FBT. Discussions of calories and the use of calorie targets to guide renourishment are generally discouraged in ED treatment settings in an effort to decrease preoccupations with calorie counting. Building upon this hypothesis, Plate-by-Plate authors cite the following rationale for use of a visual approach: (1) informed by a study that found an association between calorie-tracking application use and either maintenance or worsening of ED symptoms [31], authors hypothesized that a visual and simplistic versus numbers-based approach may have a beneficial influence on eating disorder symptoms and would allow for a seamless transition to “normal,” independent eating in later stages of treatment and beyond. Further, any calorie counting done by caregivers may “trickle down” to the patient and may thereby reinforce or exacerbate ED symptoms or thoughts. (2) A visual approach offers more flexibility by accommodating dietary restrictions, culturally appropriate food preferences, and easy adaptation for meals and snacks consumed outside of the home. (3) Given the lack of nutritional guidance due to exclusion of RDs in early FBT models, Plate-by-Plate was created to help parents with refeeding efforts using a more specialized approach, while still honoring the “parental empowerment” tenant central to FBT by allowing parents to select foods served.

With this study, we aim to test and challenge these assumptions through direct comparisons with a calorie-based approach. As part of standard practices at Equip Health, digital “food journals” (ie, photos and descriptions of foods) are provided by caregivers for assessment by RDs. In the absence of photos, the calorie-based approach allows parents to share calorie totals, which we suspect offer a more precise estimate of intake, and are less subject to parent interpretations and verbal description of portions or foods served and consumed. A calorie-based target may offer flexibility in “how” needs are met, and, like Plate-by-Plate, honors cultural preferences and dietary restrictions. We will further test the assumption that calorie targets trickle down to the patient, as caregivers are explicitly instructed not to share calorie information with patients, and ED patients have an existing general awareness of calorie content of foods and are able to quickly estimate upon provision of a meal or snack. Further, it is common practice in FBT to encourage parents to prepare and plate foods without the child present to minimize negotiations, resistance, and opportunity for patients to scrutinize components or portions.

### Participant Selection

The decision was made to exclude ED subtypes other than AN and ARFID for the following reasons:

Need for weight restoration was an important part of the inclusion criteria as weight restoration is typically first priority and a core component of ED treatment. Given that we are less likely to encounter a need for weight restoration in other ED subtypes, and would thus yield a small sample size within those subtypes, we opted to include only patients with AN and those with ARFID, which are the primary presenting subtypes in our patient population. In addition, while caregiver feedback is important, various aspects of FBT can be challenging for caregivers. We felt it important to have an outcome measure (weight) that is most predictive of remission and success with FBT.In addition to there being little research on dietary interventions in the ED space in general, research looking at dietary interventions for ARFID, and particularly for patients undergoing FBT, is especially sparse. Given the differences in symptoms and presentation between patients with ARFID and those with AN, we felt it is important to better understand the benefits and challenges associated with the use of a visual approach. For example, patients with ARFID may present with a very limited number of acceptable foods and the lack of variety may make it challenging for parents to present meals or snacks with multiple components from numerous food groups. It is our hope that the outcome data, coupled with rich insights from clinicians and caregivers, will help us understand which aspects of our interventions may be most appropriate for patients with ARFID, and the ways in which they differ from patients with AN.

## Discussion

### Strengths and Limitations

To our knowledge, this will be the first comparison of digitally delivered dietary interventions for the treatment of EDs. Given access issues faced by patients seeking ED treatment, and increasing acceptability and use of telehealth, it is of particular value to test interventions in the digital space. Testing assumptions upon which approaches are developed is also valuable as we were able to gain insights that help us tailor approaches that better resonate with caregivers and providers.

It should be noted that the majority of patients who present for ED treatment at Equip have engaged with numerous prior programs and providers, and as such, they may have encountered various dietary approaches. While it was not realistic nor warranted to exclude those with prior treatment histories, we addressed this by instructing RD interventionists to notify study personnel should it prohibitive to orient caregivers to the assigned approach. At that point, a determination will be made as to whether the patient should be withdrawn from the study. Further, although with FBT caregivers are tasked with renourishing their child between ages 6 and 24 years, it is possible that there may be differences in intervention across age ranges, particularly for patient-facing interventions. However, it should be noted that individual (patient) nutrition therapy is provided only in later stages of FBT (generally following several months of nutritional restoration).

### Future Work

In this study, we compare 2 digitally delivered dietary interventions most commonly used by dietitians in eating disorder treatment settings and subsequent outcomes. Future research is needed to examine the effectiveness of interventions delivered directly to patients and across the broad range of ED subtypes.

## Appendix

Multimedia Appendix 1 Semistructured registered dietitian interventionist interview script.

Multimedia Appendix 2 Semistructured caregiver interview script.

Multimedia Appendix 3 Overview of Plate-by-Plate approach.

## Abbreviations

AN: anorexia nervosa
ARFID: avoidant restrictive food intake disorder
ED: eating disorder
FBT: family-based treatment
RD: registered dietitian
